###### Measure 2 (avoidable/unavoidable ED attendance)

Index events that resulted in conveyance to ED will be classified according to whether they resulted in an AA or not.

To determine this, the events will be assessed against O’Keeffe *et al*’s^9^ definition. Namely, a person has been involved in an AA if routine hospital coding for the attendance indicates it did not result in the person being investigated (except urinalysis, pregnancy test, dental investigation) or treated (except prescription, recording vital signs, dental treatment or guidance/advice), and they were discharged.

O’Keeffe’s system has advantages. It is generic, applicable to all ages,^9 70^ based on process of care rather than initial triage score and has been adopted by the NHS.^71^ It is also quick and routine data have been found to be sufficient to mean it can be applied to ~98% of attendances.^9^

A possible disadvantage is it assumes *all* investigations, treatments and admissions were clinically indicated. Some may have happened for other reasons (eg, routine or inappropriate administration of test). Thus, we shall describe the reasons why any WP1a cases satisfied the criteria for an unavoidable attendance. Moreover, via WP1b, we shall ask ED clinicians to what extent suspected seizure cases attending their EDs could satisfy the criteria of an unavoidable attendance based on routine practice. Should it prove warranted, a sensitivity analysis will be conducted with and without such cases.

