**Ethics and dissemination:**

WP1a and WP2 will be conducted under database ethical approval (IRAS 307353) and Confidentiality Advisory Group (22/CAG/0019) approval. WP1b and WP3 have approval from the University of Liverpool Central Research Ethics Committee (11450). We shall engage in proactive dissemination and knowledge mobilisation to share findings with stakeholders and maximise evidence usage.

STRENGTHS AND LIMITATIONS OF THIS STUDYRisk of Adverse Outcomes after a Suspected Seizure will use a ‘cutting-edge’ linked data set that captures service use in one ambulance region using data high in quality and coverage.The parameters of the outcome measures used to describe risks and the variables tested for their ability to predict these outcomes will be informed by stakeholders and service users.The large, pseudoanonymised nature of the linked data set will require the use of a generic definition of an ‘avoidable attendance’ whose validity for suspected seizures is not yet known.As there are no equivalent linked data sets available for other ambulance regions, the validity of the derived prediction models will need to be determined within a cohort of patients treated within the same region, but at a later date.

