### Current project

#### Overview and aims

To address the identified needs and information gaps, the 24-month mixed-methods RADOSS project is being completed. It has the following aims: (1) calculate the risks and benefits of conveyance to hospital after a suspected seizure; (2) create a risk prediction tool that predicts the likelihood that an individual will die and/or recontact the UEC system within 3 (and 30) days if not conveyed and the likelihood that their conveyance to ED would result in an AA; and (3) establish a pathway to clinical implementation of the risk prediction tool and maximise usage of RADOSS findings. The project’s related objectives were noted in table 1.

**Table 1 T1:** The RADOSS project’s aims and objectives and the work packages that address them

Aims	Objectives
(1) Calculate the risks and benefits of conveyance to hospital after a suspected seizure.	a. Describe the characteristics of those conveyed and those not conveyed to ED by one representative English ambulance service (WP1a).
	b. Compare the proportions following conveyance and non-conveyance that die and/or recontact the UEC within 3 (and 30) days (WP1a).
	c. Quantify the proportion of incidents conveyed to ED that meet the definition of an AA (WP1a).
(2) Create a risk prediction tool that predicts the likelihood that an individual will die and/or recontact the UEC system within 3 (and 30) days if not conveyed and the likelihood that their conveyance to ED would result in an AA.	d. Optimise the prediction tool development by completing KE workshops with service users and ambulance and ED clinicians to get views on predictors considered for inclusion in the models, the way the outcome measures of death, UEC recontact and AA are defined and risk score presentation (WP1b).
	e. Develop statistical models to predict a person’s risk of death/recontact with the UEC system within 3 (and 30) days and the likelihood of their attendance at ED being classed an AA if conveyed (WP1a).
	f. ‘Temporally’ validate the predictive models using data from the same ambulance service for a later time period (WP2).
(3) Establish a pathway to clinical implementation of the risk prediction tool and maximise usage of RADOSS findings.	g. Complete ‘next steps’ workshops with stakeholders to finalise plans to refine the tool for clinical use and its evaluation (WP3).
	h. Complete a proactive dissemination and knowledge mobilisation strategy (WP3, WP4).

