##### Sample size

Predictive models for the (1) risk of death/UEC recontact following conveyance, (2) risk of death/UEC recontact following non-conveyance, and (3) risk of an AA following conveyance could be developed. To permit robust testing of at least 40 candidate predictor parameters for each of these models, Riley *et al*’s^72^ formulae using standard parameters indicate: for model (1), a need for 2567 index events, with 103 experiencing the target event; for model (2), a need for 2194 index events, with 308 experiencing the target event; and for model (3), up to 2194 index events, with 461 experiencing the target event. Twelve months of YAS data should be sufficient to satisfy these requirements. Online supplemental file 3 details the reasons why and provides further information on the sample size calculation.

10.1136/bmjopen-2022-069156.supp3Supplementary data

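### As worded, the sensitivity analysis for routine ED practice excludes the doubtful attendances; recoding them as avoidable would address the misclassification the plan describes

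*Protocol article*

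**What the plan says.** Under Measure 2, an attendance is avoidable if routine coding shows no investigation and no treatment, apart from listed exceptions, and the patient was discharged. The same section concedes that this treats every investigation, treatment and admission as clinically indicated: "Some may have happened for other reasons (eg, routine or inappropriate administration of test"). It plans two responses before any re-analysis. The reasons for unavoidable status will be described, and ED clinicians in WP1b will be asked how far seizure cases "could satisfy the criteria of an unavoidable attendance based on routine practice". Then comes the conditional step: "Should it prove warranted, a sensitivity analysis will be conducted with and without such cases".

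Two other places fix the target. Objective c in Table 1 is to "Quantify the proportion of incidents conveyed to ED that meet the definition of an AA (WP1a"), so the denominator is all incidents conveyed to ED; the section on describing sample and patient outcomes uses the same denominator. The Sample size section makes AA following conveyance the outcome of model 3. The strengths and limitations box says the AA definition is one "whose validity for suspected seizures is not yet known".

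**The concern.** The problem the section describes is one of classification: an attendance carries the label unavoidable when, on clinical grounds, it may have been avoidable. The cases in question are all coded non-AA. Taking them out leaves the AA count as it was and shrinks only the denominator. The result is the AA proportion among attendances whose label is not in doubt, a different quantity from objective c. It also falls strictly between the as-coded figure and the figure with the labels changed (unless every non-AA case is routine-only), so it marks neither end of the range that the doubt creates.

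For model 3 the same step removes records according to their coded outcome. A refit on what is left would give absolute AA risks that do not apply to the conveyed population, and absolute risk is what the draft tool is meant to display. A reader using the sensitivity analysis to judge how far routine testing affects the AA result would be told the effect is smaller than full recoding would show.

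**Working it through.** **Inputs.** The Sample size section gives: "for model (3), up to 2194 index events, with 461 experiencing the target event". The article does not give the share s of coded-unavoidable attendances that are there only through routine practice, so s is assumed below.

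**The plan's figure.** 461/2194 = 21.0%. The sample size reproduces with 40 parameters under the Riley shrinkage criterion, taking S = 0.90 and Cox-Snell R² = 0.15 (both assumed; the article says only that standard parameters were used):

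n = 40 / [(0.90 − 1) × ln(1 − 0.15/0.90)] = 40 / 0.01823 = 2194 (rounded up)

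events = 0.21 × 2194 = 460.7, rounded up to 461.

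The same inputs reproduce model 2 (2194 and 308) and model 1 (2567 and 103; there the R²-optimism criterion governs). The sample-size figures are sound on this point, and 21% is the planning value for AA.

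**Exclusion against recoding.** Let N = 2194, A = 461 and k = s × (N − A) = s × 1733.

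- Excluded: A/(N − k)
- Recoded: (A + k)/N
- Recoded minus excluded = k(N − A − k) / [N(N − k)]

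The difference is positive for any k between 0 and N − A, and zero only if no case, or every non-AA case, is routine-only.

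| Assumed s | k | Excluded | Recoded | Gap |
|---|---|---|---|---|
| 10% | 173 | 461/2020.7 = 22.8% | 634.3/2194 = 28.9% | 6.1 points |
| 25% | 433 | 461/1760.75 = 26.2% | 894.25/2194 = 40.8% | 14.6 points |
| 50% | 866 | 461/1327.5 = 34.7% | 1327.5/2194 = 60.5% | 25.8 points |

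Because AA requires discharge, an admitted patient cannot be recoded. The share s is therefore capped by the fraction of the 1733 who were discharged, which the article does not give. The 50% row needs at least half of them to have been discharged and is shown only for the shape of the relation.

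**Model 3.** Suppose the routine-only cases are all truly avoidable and routine testing is unrelated to the predictors. Dropping them then under-samples avoidable cases by the factor A/(A + k), which shifts the logistic intercept by ln[A/(A + k)] and leaves the slopes alone:

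- s = 10%: ln(461/634.3) = −0.32
- s = 25%: ln(461/894.25) = −0.66

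A simulation with one predictor, true slope 1.0 and 1,000,000 records agrees. At 10% the true intercept was −1.08 and the exclusion fit gave −1.40; mean predicted AA risk over the full conveyed cohort was 0.236 against a true 0.289. At 25% the intercepts were −0.45 and −1.12, and the mean risks 0.283 and 0.408. The slope stayed at 1.0. If routine testing depends on the predictors, slopes can be biased too.

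Exclusion also reduces the sample: about 2021 records remain at 10% and 1761 at 25%. Recoding keeps 2194.

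**The case against.** The strongest reply is that the sentence never says the cases leave the denominator. It sits in a section about how events are classified, and running the analysis without such cases could be shorthand for not counting them as unavoidable. Usage elsewhere is mixed. The end-of-life item under Measure 1 and the refusal item under describing sample and patient outcomes both take people out. The recontact item in that same section, which concerns later contacts meeting the AA definition, can be read as deciding which contacts count. So a reader might infer that the authors have firmly chosen exclusion; the text does not go that far. What stands is that exclusion is the plain reading, that no sentence provides for recoding, and that two analysts could obtain materially different AA figures from the same words.

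A reader might also infer that this is the only safeguard on the AA definition. It is not. The reasons for failing the definition are tabulated unconditionally, the WP1b topic guide asks whether routine ED practice disqualifies seizure cases by default, and WP1b may inform the definition itself. These are partial checks; none of them re-estimates the AA proportion.

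The detailed code list belongs in an analysis plan and cannot exist before WP1b. That is accepted, and its absence is not the point. The point is the kind of re-analysis the article names.

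Exclusion is not worthless either. In the simulation the as-coded slope was attenuated (0.85 at 10%, 0.67 at 25%) and exclusion restored it to 1.0. The loss is in the proportion and the intercept.

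Finally, recoding is not simply the truth. A test done routinely may still have been indicated, so recoding every such case is an upper-bound assumption.

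**Conclusion.** The concern holds in a limited form. On its plain reading the sensitivity analysis excludes coded non-AA cases, which does not estimate the AA proportion among all conveyed incidents and understates what that proportion would be if those cases counted as avoidable. A model 3 refit on the reduced sample would have a biased intercept. The direction is certain on that reading, provided at least one non-AA case is not routine-only. The size is not known: 6.1 points at an assumed 10% share and 14.6 points at 25%, starting from a planning value of 21% that is not an observed proportion, with the share capped by the number discharged.

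Two stronger conclusions are not supported. The primary AA proportion and the primary model 3 are unaffected, and nothing says a sensitivity refit would enter the draft tool, which combines the three derived models. Making the analysis conditional on the WP1b findings is also a legitimate choice; running it regardless would be a preference, not a correction.

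**What to change.** Replace the sensitivity-analysis sentence with one to this effect: in the sensitivity analysis, discharged attendances whose only disqualifying codes are on a list of routine seizure investigations or treatments, agreed from WP1b and fixed before modelling, will be recoded as AA and kept in the denominator; the AA proportion, and any model 3 refit, will be reported under both the as-coded and the recoded definitions. Add that the recoded result is an upper bound, because some routine tests may have been clinically indicated. An exclusion run may be kept as a supplement if it is labelled as the proportion among attendances whose class is not in doubt.

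The cost is a sentence or two and a recode of data already in the extract. The reasons for unavoidable status are already to be tabulated and ED clinicians are already to be asked about routine practice, so no new data are needed. If the authors meant recoding all along, the change only makes that explicit.

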##### Sample size

Predictive models for the (1) risk of death/UEC recontact following conveyance, (2) risk of death/UEC recontact following non-conveyance, and (3) risk of an AA following conveyance could be developed. To permit robust testing of at least 40 candidate predictor parameters for each of these models, Riley *et al*’s^72^ formulae using standard parameters indicate: for model (1), a need for 2567 index events, with 103 experiencing the target event; for model (2), a need for 2194 index events, with 308 experiencing the target event; and for model (3), up to 2194 index events, with 461 experiencing the target event. Twelve months of YAS data should be sufficient to satisfy these requirements. Online supplemental file 3 details the reasons why and provides further information on the sample size calculation.

10.1136/bmjopen-2022-069156.supp3Supplementary data

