##### Sample size

The validation sample will be similar to that used for derivation. It will thus satisfy the recommendation that validation samples include ≥200 cases experiencing the target events.^92 93^

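### The three sample sizes imply one Cox–Snell R² of 0.15 for every model, which makes the stated minimum for model 1 (2567 patients, 103 events) too small for 40 candidate parameters

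*Protocol article*

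**What the plan says.** The WP1a sample size section sets its aim as follows: "To permit robust testing of at least 40 candidate predictor parameters for each of these models". It cites published formulae for prediction-model sample size and says that these "formulae using standard parameters indicate" three needs:

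- Model 1, death or recontact after conveyance: "for model (1), a need for 2567 index events, with 103 experiencing the target event".
- Model 2, death or recontact after non-conveyance: "for model (2), a need for 2194 index events, with 308 experiencing the target event".
- Model 3, avoidable attendance after conveyance: "for model (3), up to 2194 index events, with 461 experiencing the target event".

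It concludes: "Twelve months of YAS data should be sufficient to satisfy these requirements". No R², shrinkage target or event rate is printed. For these the reader is sent elsewhere: "Online supplemental file 3 details the reasons why and provides further information on the sample size calculation". That file is not among the documents at hand.

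**The concern.** Models 2 and 3 have the same required size although their event counts imply different event rates (14% and 21%). That would not happen if each model's expected R² had been set relative to what is attainable at its own event rate. It points to one absolute R² used throughout.

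This matters because the maximum Cox–Snell R² falls steeply as the outcome becomes rarer. A fixed value that is moderate at 21% is very demanding at 4%. A higher assumed R² gives a smaller required sample, so the rare-outcome model gets a minimum that is too easy to meet.

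The stated needs are the article's basis for admitting 40 or more parameters in each model. If they serve as the benchmark, model 1 could be judged adequately supplied when it is not. Its estimates would then be more overfitted than the chosen criterion is meant to allow, and they feed a tool intended to inform conveyance decisions.

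**Working it through.** **Inputs**

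- From the WP1a sample size section: P = 40 parameters, with sizes and events of 2567 (103), 2194 (308) and 2194 (461). The implied event rates are 103/2567 = 0.040, 308/2194 = 0.140 and 461/2194 = 0.210.
- Assumed, because not printed: target shrinkage S = 0.90, optimism in R² of 0.05 relative to its maximum, and a margin of 0.05 for the overall risk.
- Back-solved: R².

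**Formulae** (φ = event rate, R² = Cox–Snell)

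- Maximum: R²max = 1 − exp{2[φ ln φ + (1 − φ) ln(1 − φ)]}
- Criterion 1: n = P / [(S − 1) ln(1 − R²/S)], S = 0.90
- Criterion 2: the same expression with S = R² / (R² + 0.05 R²max)
- Criterion 3: n = (1.96/0.05)² φ(1 − φ)
- The required n is the largest of the three.

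**Step 1. Reproduce the plan with R² = 0.15**

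- Criterion 1, any model: 40 / [−0.1 × ln(1 − 0.15/0.9)] = 40 / (0.1 × 0.18232) = 2193.9, so 2194.
- Criterion 2, model 1: R²max = 0.2853, S = 0.15 / (0.15 + 0.01426) = 0.9132, n = 2566.9, so 2567. For models 2 and 3 it gives about 1309 and 1128, so criterion 1 governs there.
- Criterion 3 gives about 59, 185 and 255 and never governs.
- Events: 2567 × 0.04 = 102.7, 2194 × 0.14 = 307.2 and 2194 × 0.21 = 460.7, which round up to 103, 308 and 461.

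All six printed figures match. With these settings, only R² = 0.150 (to three decimals) gives 2194 under criterion 1. A common fraction of the maximum would give models 2 and 3 different sizes.

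**Step 2. What 0.15 means in each model**

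| Model | φ | R²max | 0.15 / R²max | C-statistic (normal linear predictor, simulated) |
|---|---|---|---|---|
| 1 | 0.04 | 0.285 | 53% | about 0.95 |
| 2 | 0.14 | 0.555 | 27% | about 0.81 |
| 3 | 0.21 | 0.642 | 23% | about 0.77 |

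**Step 3. Required n with R² set as a fraction of its maximum (P = 40)**

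| Fraction of maximum | Model 1 (stated 2567) | Model 2 (stated 2194) | Model 3 (stated 2194) |
|---|---|---|---|
| 10% | 12418 | 6284 | 5403 |
| 15% | 8211 | 4121 | 3534 |
| 20% | 6108 | 3039 | 2598 |
| 25% | 4845 | 2389 | 2036 |
| 30% | 4003 | 1955 | 1661 |
| 40% | 2951 | 1412 | 1191 |
| 50% | 2578 | 1208 | 1010 |

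Example, model 1 at 15%: R² = 0.15 × 0.2853 = 0.0428; n = 40 / [−0.1 × ln(1 − 0.0428/0.9)] = 40 / (0.1 × 0.04872) = 8211 (329 events, rounded up).

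**Step 4. Rough supply from the article's own figures**

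Table 2 gives about 211,000 calls a year in England and about 70% conveyed. Table 3 gives 10 services and about 85% linkable. Table 4 gives 90% aged 16 or over. Assuming an average-sized service:

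- 211,000/10 × 0.90 × 0.85 ≈ 16,140 linked adult incidents
- conveyed: 0.70 × 16,140 ≈ 11,300
- not conveyed: 0.30 × 16,140 ≈ 4,840

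These are incidents. The note to Table 4 makes the patient's first episode the unit of analysis, so patient counts will be lower by an amount the article does not give. Against the 15% needs, model 2 falls short once repeats exceed 1 − 4121/4842 ≈ 15% of non-conveyed incidents. For model 1 the figure is 1 − 8211/11299 ≈ 27% of conveyed incidents.

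**The case against.** **The R² is not in the article.** Supplemental file 3 may state and justify it, and any replacement benchmark, such as 15% of the maximum, also comes from outside the documents. This stands as far as it limits the size of the claim. A reader might infer that all three needs are too small by factors of about 1.6 to 3.2 (3534/2194 to 8211/2567). The documents do not support that: the factors hold only if 15% of the maximum is the right value. At 25%, model 2 is 1.09 times its stated size and model 3 already below it; at 30% both are below. What survives is model 1, whose need exceeds 2567 at every fraction tested from 10% to 50%. The file could explain the choice of inputs, but it could not change what they imply about model 1.

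**The stated sizes are minima.** The cohort takes every eligible patient in 12 months. A reader might infer that the models will be badly overfitted, because at 15% of the maximum a sample of 2567 would give model 1 an expected shrinkage of 0.74. That applies only if the team stopped at the minimum, and nothing says it will. The supply estimate exceeds even the 15% needs before reduction to patients, so the statement that 12 months suffices is not shown to be false.

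**WP2.** A reader might also infer that a derivation need of 103 events contradicts the WP2 sample size claim, "It will thus satisfy the recommendation that validation samples include ≥200 cases experiencing the target events". It does not. That section compares the validation sample with the derivation sample actually used. At 4% of about 11,300 conveyed incidents there would be about 450 model 1 events before reduction to patients. More than about 55% of conveyed incidents would have to be repeats (1 − 5000/11299) before the count fell below 200.

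**Safeguards.** The plan repeats the whole modelling process in 500 bootstrap samples, shrinks the coefficients, and validates in a later period with recalibration if needed. These limit the harm. They do not replace an adequate sample or stabilise predictor selection.

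**Conclusion.** The point holds, chiefly for model 1. The printed figures imply a flat Cox–Snell R² of 0.15. For an outcome at 4% this is 53% of the attainable maximum and a C-statistic of about 0.95. The article says that no prediction tools relating to non-conveyance exist yet and describes the evidence on predictors as exploratory, so nothing in it supports such a value. The stated minimum of 2567 (103 events) is therefore too small for 40 parameters. The need is 4003 to 12418 across 30% down to 10% of the maximum, and still 2951 at 40%.

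For models 2 and 3 the finding is sensitivity, not error. The needs range from 4121 and 3534 at 15% to 2389 and 2036 at 25%, against 2194 stated.

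The conclusion rests on the back-solved R², on shrinkage of 0.90 and optimism of 0.05, and on event rates read from the printed counts. The C-statistics also assume a normal linear predictor. Whether the actual data fall short is unknown; model 2 is the tightest on the article's own supply figures.

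**What to change.** 1. In the WP1a sample size section, state R² for each model as a fraction of its maximum Cox–Snell R² at the expected event rate, with the reason for the fraction. State the shrinkage and optimism targets too.
2. Recompute and restate the three needs. If 15% is assumed, they are 8211 (329 events), 4121 (577) and 3534 (743).
3. Replace the promise of at least 40 parameters for each model with a cap per model, set from the actual linked count of one record per patient and fixed before any outcome–predictor analysis. At 15% of the maximum this is one parameter per about 205 conveyed patients (model 1), 103 non-conveyed (model 2) and 88 conveyed (model 3). Another fraction changes these ratios.
4. Optionally, state the validation need per model in the WP2 sample size section and check it against the actual count. At 4%, 200 events need about 200/0.04 = 5000 conveyed patients.

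The cost is a change of text and a short recalculation, with no extra patients. The downside is a less favourable stated requirement and possibly fewer candidate parameters, most likely in models 1 and 2.
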